## Abstract

**Background:**

Late diagnosis of HIV fosters HIV transmission and may lead to hidden HIV epidemics. In Belgium, mathematical modeling indicates a high prevalence of undiagnosed HIV infections among men who have sex with men of non-Belgian origin and among sub-Saharan African migrants. Promotion of HIV testing facilitates early diagnosis, but diagnostic opportunities are missed in primary care.

**Objective:**

The intervention study aims to enhance provider-initiated HIV testing by GPs. This protocol presents the conceptual development, implementation, and evaluation of an HIV-testing intervention for Flemish general practitioners (GPs).

**Methods:**

A mixed methods evaluation design is used. Guided by a simplified intervention mapping approach, an evidence-based intervention was developed in collaboration, guided by an interdisciplinary advisory board. The intervention consisted of an evidence-based tool (ie, “HIV-testing advice for primary care”) to support GPs in provider-initiated HIV testing. A modified stepped-wedge design compare two different intervention levels: (1) online dissemination of the HIV-testing advice and (2) dissemination with additional group-level training. Both conditions were compared against a control condition with no intervention. The effect of the intervention was measured using Poisson regression for national surveillance data. The primary outcome was the number of HIV diagnoses made by GPs. Secondary outcomes were HIV diagnoses among groups at risk for undiagnosed HIV, distribution of new diagnoses by CD4 cell count, number of HIV tests prescribed by GPs, and rate of new diagnoses by tests. To evaluate the intervention’s implementation, the GPs’ fidelity to the intervention and the intervention’s feasibility and acceptability by GPs were assessed through (web-based) surveys and in-depth telephone interviews.

**Results:**

The study was funded in 2016 and ethically approved in January 2017. The implementation of the intervention started in January 2017 and ended in December 2018. Data was completed in October 2019 and was the starting point for the ongoing data analysis. The results are expected to be published in the second half of 2020.

**Conclusions:**

Results of the intervention study will provide useful information on the intervention’s effectiveness among Flemish GPs and can inform further development of official testing guidelines. Limitations of this real-life intervention approach are potential spill-over effects, delay in access to surveillance data, and little detailed information on HIV-testing practices among GPs.

**Trial Registration:**

ClinicalTrials.gov NCT04056156; https://clinicaltrials.gov/ct2/show/NCT04056156

**International Registered Report Identifier (IRRID):**

DERR1-10.2196/16486

## Introduction

HIV-positive individuals who are unaware of their status have a higher risk of transmitting HIV [1], potentially fueling a hidden HIV epidemic. HIV testing is a crucial step in HIV prevention continuum facilitating timely HIV diagnosis [2]. However, in 2017, about half of the HIV patients newly diagnosed in countries that belong to the European Union/European Economic Area with a known CD4 cell count were diagnosed late (CD4 cell count<350 cells/mm^3^); 28% were diagnosed at an advanced stage (CD4 cell count<200 cells/mm^3^) [3]. In Belgium, two key populations are most affected: men who have sex with men (MSM) and sub-Saharan African Migrants (SAMs) [4]. More than a third of new Belgian HIV cases were diagnosed late in 2017, ranging from 27% among MSM to 50% among SAMs.

The *HIV European Research on Mathematical Modeling and Experimentation of HIV Testing in Hidden Communities* (HERMETIC) project applies a mathematical model for routine HIV-surveillance data to calculate the size and proportion of these undiagnosed HIV-infected populations. Modeling results obtained using a back-calculation method [5] for Belgium indicate that almost 2818 people living with HIV remained undiagnosed in 2015, corresponding to a prevalence rate of 4.1 undiagnosed persons per 10,000 [6]. The most affected populations were non-Belgian MSM (almost 264 undiagnosed persons per 10,000), SAMs with a higher proportion among women (about 173 per 10,000) than among men (about 93 per 10,000), and Belgian MSM (about 55 per 10,000) [6]. While Belgian HIV-testing rates are relatively high and cost-effective with 1.25 new HIV diagnoses per 1000 tests [4,7], these estimates of undiagnosed HIV infections indicate that current HIV-testing strategies fail to reach all people at risk of infection in a timely manner.

General practitioners (GPs) are well placed to facilitate early HIV diagnoses; their long-term and holistic relationships with patients provide opportunities for HIV testing, as they are the first entry point to health care [8-10]. However, many diagnostic opportunities are missed in primary care [11-13]. A recent systematic review showed the following GP-specific barriers and facilitators: lack of time, fear to disturb the consultation process, language barriers, lack of culture-sensitive sexual counseling skills, and concerns about pretest discussion or result management [11]. GP-specific training and practical tools to support HIV testing were found to facilitate HIV testing in primary care. Earlier research mentions similar barriers among Belgian GPs [14]. A recent analysis on Belgian surveillance data has shown that Belgian GPs predominantly diagnose MSM, whereas SAMs are more often diagnosed by specialists [15]. The fact that about half of all HIV tests conducted in Belgium in 2017 were prescribed by GPs [4] and that complementary community-based testing initiatives are in place [16,17] indicates the potential to increase the HIV-testing offer in primary care.

To identify solutions to these barriers and reduce the hidden HIV epidemic in Belgium, we developed an HIV-testing intervention for primary care by adopting a simplified intervention mapping approach [18,19] (Figure 1). This approach was chosen to ensure appropriateness and future sustainability, as it promotes the use of theory and evidence, as well as the inclusion of stakeholders [18]. Collaborative participation [20] was ensured through an advisory board consisting of 22 experts including GPs, representatives of GP umbrella organizations, policy makers, HIV care specialists, public health specialists, prevention specialists, and lab specialists. The advisory board has been consulted at all stages of the research, providing inputs to content and strategic decisions.

In the preparatory phase, a detailed contextual analysis of the problem within the local Flemish context was conducted (see step 1 in Figure 1). The aforementioned modeling results [6] were triangulated with multiple data sources [21], such as behavioral surveys and an expert meeting for validation and to gain further in-depth insight. The results of a mixed research synthesis on HIV testing in European general practices [11] provided additional guidance. The advisory board selected two evidence-based HIV-testing strategies to be further elaborated for this intervention: provider-initiated testing of key populations and indicator condition–based testing. A participatory, formative research with 122 GPs using group discussions was conducted to obtain their inputs on the acceptability and feasibility of these strategies [22]. While the two proposed testing strategies were generally accepted by the participants, deficits in knowledge about relevant HIV epidemiology and skills to propose testing became apparent. GPs emphasized on the lack of official policy guidelines to support them in provider-initiated HIV testing.

On the basis of the results of the preparatory phase, it was decided in collaboration with the advisory board that the intervention should integrate the two assessed HIV-testing strategies into one intervention consisting of a GP-specific HIV-testing tool for providing information and an accompanying group-level training that practically supports GPs in performing provider-initiated HIV testing. Here, we present the HERMETIC study protocol for the intervention’s content development, and the practical strategies for implementation and evaluation in Flanders, Belgium (steps 2, 3, 4, 5, and 6 in Figure 1).

**Figure 1 figure1:**
[figure not shown]
Developing an HIV-testing intervention for Flemish GPs. A stepwise approach to intervention development 19.

## Methods

Figure 2 shows a schedule of the enrollment, intervention, and evaluation of the HIV-testing intervention.

**Figure 2 figure2:**
[figure not shown]
Schedule of enrolment, allocation, intervention, and evaluation of the HIV-testing intervention.

### Objectives and Outcomes

The objective of the study is to evaluate the effectiveness of two different intervention levels (dissemination of the information tool and group-level training) against a control condition. This will be assessed by the following primary and secondary outcomes:

Primary outcome measure is the number of HIV diagnoses made by the GPs. We will evaluate the change in the number of new HIV diagnoses made by GPs by comparing the data from 2016, which serve as baseline data, to data from 2017 and 2018.Secondary outcome measures are HIV diagnoses among groups identified to be more likely undiagnosed, distribution of new diagnoses by CD4 cell count (to assess changes in late HIV diagnoses), the overall number of HIV tests prescribed by GPs, and the rate of new diagnoses by the number of HIV tests performed.

To evaluate the intervention’s implementation, GPs’ fidelity to the intervention and its perceived feasibility and acceptability by GPs are assessed using mixed methods (see “Methods” section).

### Study Population

The study aims to enroll all Flemish GPs who are affiliated to a *“GP circle” (ie, huisartsenkring or HAK)*. The *HAK* is the local focal point for GPs and policy makers to implement health policy in primary care, and provides continuous medical education [23]. HAKs are subsidized by the Flemish government and are organized by geographical zones. In 2016, 8163 GPs were active in Flanders [24]. Among them, 6211 (76.1%) are affiliated to one of the 86 HAKs (Zorg en Gezondheid, personal communication via email, September 2016). The choice of enrolling only GPs affiliated to a HAK is a pragmatic one: GPs can be easily accessed through HAKs, and the geographical aspect provides an opportunity for nonindividual comparison. No data are available to describe GPs who are not affiliated to HAKs, but they are assumed to be mainly working in nonprimary care contexts such as specialist centers for educational health care (Zorg en Gezondheid, personal communication via email, September 2016).

### Intervention Content and Practical Strategies

The findings of HIV knowledge gaps and testing skills as determinants among GPs during the formative research [22] led to the selection of the empirically widely tested i*nformation-motivation-behavioral skills model* [25] as a theoretical base for the intervention’s content, practical strategies, and implementation (see steps 2 and 3 in Figure 1). To meet GPs’ demand for official guidelines, the intervention should include dissemination of an HIV-testing advice and a group-level training (step 4 in Figure 1).

#### HIV-Testing Advice

User-friendly advice combining the two selected HIV-testing strategies was created (see Figures 3 and 4). Informed by the expressed needs of GPs during the formative research, it guides them in proactively testing patients at heightened risk of HIV acquisition and patients presenting with an HIV-indicator condition and gives a time indication of how often an HIV test should be performed. National epidemiological information and the HERMETIC modeling results have defined the key target groups that an HIV test should be offered to. The extensive 64 HIV-indicator conditions formulated in the HIV Indicator Diseases Across Europe Study [7] were reduced to 14 conditions often diagnosed in primary care, as indicated by the formative research results and in collaboration with the AB [22]. The advice also provides country-specific information on HIV prevalence as an additional rationale as to why targeting patients at heightened risk due to migration from high endemic regions is recommended.

**Figure 3 figure3:**
[figure not shown]
Advice HIV-testing by GPs (front side).

**Figure 4 figure4:**
[figure not shown]
Advice HIV-testing by GPs (back side).

#### Group-Level Training

GPs expressed their preference for a face-to-face training as an intervention delivery channel [22]. To increase GPs’ motivation and skills on HIV testing, we designed a group-level training for 1.5-2 hours, consisting of three main parts, each led by trainers with different types of expertise. The introduction given by a public health expert discusses current HIV epidemiology, advantages of early diagnosis, missed opportunities in primary care, current HIV-prevention approaches and GPs’ role in these, and common misconceptions about HIV risk. The second part presents the HIV-testing advice in detail. An HIV specialist provides specific medical information (ie, on the indicator conditions). The third part given by an HIV-prevention worker focuses on the use of the advice including aspects of patient-provider interaction and communication skills. In the latter part, specific tips and reference to hands-on tools were given to overcome the barriers related to the specific target groups (such as using the visual online support tool Zanzu [26] to reduce language- or culture-related barriers).

### Intervention Implementation

Two intervention levels were established, differing in terms of degree of information delivered and delivery channels. For the latter, the existing GP channels were selected: the website of the GP umbrella organization [27] and HAK networks. At the third level, the control condition, GPs receive no intervention, that is, they are not actively targeted according to the current standard practice.

#### Intervention Level 1: Online Dissemination of the HIV-Testing Advice

GPs included at the first level receive the HIV-testing advice through an email by their HAK coordinator, which contains an information message with the printer-friendly version of the HIV-testing advice attached (see Figures 3 and 4). The message also provides a link to the website of the Flemish umbrella organization for GPs, where the tool is available for download for all Flemish GPs. A reminder is sent out to all participants after 13 months.

#### Intervention Level 2: Online Dissemination of the HIV-Testing Advice with Additional Group-Level Training Session

At the second intervention level, GPs first receive intervention condition 1 and then the face-to-face group-level training session. These sessions are organized as part of regular continuous medical education provided by HAKs at their usual venues and are organized a few months after receiving intervention level 1. A reminder of the advice is sent out 13 months after the initiation of intervention level 1.

### Study Duration

Study duration including intervention development is from January 2017 to December 2019. Intervention implementation and evaluation take place in the framework of the HERMETIC study; implementation started in December 2017 and evaluation results will be available in December 2019 (see steps 5 and 6 in Figure 1).

### Study Design

This mixed methods study adopts a modified stepped-wedge design. The classical stepped-wedge cluster design involves a random and sequential crossover of clusters from control to intervention until all clusters are exposed. It includes an initial period in which no clusters are exposed to the intervention [28]. We adopted a modified version: the two different intervention levels are added stepwise, while a control condition is retained until the end of the study period. Participants of both intervention levels serve as their own (historical) controls receiving no intervention during approximately 2 months, then all the participants receive the HIV-testing advice online. Those assigned to the first intervention level remain at this level until the end of the project. Participants assigned to the second intervention level are offered the additional group-level training after 7 months. The rationale for this adaptation is twofold: (1) to compare the effects at all intervention levels among each other over time and (2) to assess feasibility (ie, resource and time restrictions).

The process of information distribution is monitored: confirmation is obtained through short phone interviews with GP-circle coordinators to verify if the emails were sent to individual GPs and to allow for timely assessment of problems and reasons for noncompliance with the procedure.

#### Randomization Strategy

Intervention groups are identifiable in HIV-surveillance data using the administrative code referring to geographical zones defined by the National Institute of Statistics (ie, NIS code). HAKs that correspond to the same NIS code have been merged, regrouping 86 HAKs into 76 clusters. Each cluster is randomly allocated by the study team to one of the three intervention conditions using block sampling. Block sampling took the variability of the different target populations at risk for HIV in the intervention groups into consideration: each block consists of three clusters with approximately the same number of SAMs in the respective NIS-code areas. The main reason for this approach is that the intervention is assumed to generate the largest effect among SAMs, given their low testing rates in primary care. Since SAMs are unevenly distributed over Flanders with the largest communities living in central cities [29], block randomization assures that the expected effect is equally distributed across the three intervention levels. This approach results in 25 clusters being assigned to intervention level 1 or 2, and 26 clusters assigned to the control condition.

### Intervention Evaluation

A mixed methods evaluation approach is applied throughout the intervention implementation (see “Objectives and Outcomes” section and steps 5 and 6 in Figure 1). An outcome evaluation assesses the intervention’s effectiveness and changes in GPs’ targeting behavior in HIV testing using routine surveillance data on new HIV diagnoses and HIV tests performed in Flanders. Changes in the number of new HIV diagnoses made by GPs, changes in the number of diagnoses among groups at high risk for undiagnosed HIV and at different stages of HIV infection, and changes in the number of HIV tests performed by GPs and in the rate of diagnoses by tests will be assessed.

Process evaluation assesses several implementation aspects: GP’s fidelity to the intervention in addition to the intervention’s feasibility and acceptability. In intervention level 1, this will be evaluated through an online survey sent out together with an email reminder. The survey is accessible for 2 months. In intervention level 2, GPs attending the group-level trainings are registered to calculate the actual attendance rate. Sociodemographic characteristics of the trained GPs and their evaluation of the training, perceived feasibility, and acceptability of the advise are assessed by means of a structured questionnaire.

A qualitative component collects in-depth and contextual insights on perceived fidelity to the intervention, feasibility, and acceptability of the group-level intervention. It serves to understand first-hand experiences with real-life implementation, for instance, if the intervention can be implemented as designed, and aims to better understand the intervention mechanisms. Data are collected among purposively selected, trained GPs for individual telephone interviews after 5-6 months. To guide this selection, potential “rich cases” among HAKs are identified considering specific indicators assessed through the questionnaire: appreciation of group-level training, anticipated feasibility and acceptability of the advice, and impact on knowledge and skills. HAKs with the lowest, middle, and highest median scores for each of the indicators are identified, and 10% of the trained GPs per HAK are randomly selected and invited to an interview. If GPs refuse, the reason for refusal is noted and another GP from the same HAK is invited until data saturation is obtained. No postprocess evaluation from patients is planned, as previous research has shown that proactively offering an HIV test is well accepted by patients [14].

#### Data Collection

For outcome evaluation, the following routine surveillance data are used:

*National Health Insurance (Rijksinstituut voor Ziekte en Invaliditeitsverzekering [RIZIV]) data on the number of HIV tests conducted:* HIV tests are reimbursed by the Belgian National Institute for Sickness and Invalidity Insurance. Data on the number of HIV tests performed, the type of the physician requesting the test, and his/her geographical locations are available in the RIZIV database. The organization in charge of the HIV surveillance in Belgium (Sciensano, ie, the National Public Health Institute) receives extracted data on HIV tests prescribed by GPs, which will be aggregated according to the different clusters and intervention levels as identified by the NIS codes.*Laboratory data on new HIV diagnoses:* Seven national AIDS Reference Laboratories (ARL) perform HIV-confirmation tests on samples found to be reactive in screening tests in clinical laboratories. Yearly, each ARL reports data on all newly diagnosed HIV cases including sociodemographic, clinical, and limited behavioral characteristics (eg, transmission group). Sciensano links this information to the type of physician who initially prescribed the HIV test (collected through the physician’s registration number at the national social assurance system, ie, “RIZIV number”), the cluster number, and the intervention level (using the NIS codes of HAKs).

For process evaluation, data on perceived fidelity to the intervention, feasibility, and acceptability for intervention level 1 (information only) are collected through an online survey, located at the server of SoSciSurvey [30]. For intervention level 2, data are collected through a quantitative evaluation questionnaire immediately filled in on paper after the group-level training session. Data on experienced feasibility and acceptability are collected through recorded telephone interviews. In each of these data collected, limited sociodemographic characteristics of the participants are gathered, for example, age, gender, and years of experience.

#### Data Extraction and Management

For outcome evaluation, HIV-surveillance data will be transferred through technical interfaces with encrypted data to Sciensano by Healthdata, the agency responsible for data captation and secure data transfer. Data will be checked and duplicated records will be removed. Sciensano will provide the aggregated data of both HIV tests and HIV diagnoses to the researchers for further analysis.

For process evaluation, data from the online survey are collected anonymously and extracted through a downloadable Excel Database. Interview recordings will be transcribed verbatim. Pseudonymized data are managed and archived by the Institute of Tropical Medicine in locked and secured (digital) locations that are only accessible by the researchers.

#### Data Analysis and Statistical Methods

Using the stepped-wedge design, the distribution of results across unexposed observation periods is compared with that across the exposed observation periods. To determine the intervention’s effectiveness, primary and secondary outcomes at the three levels are compared against each other at three different time periods, that is, baseline and before March 2017, from March to August 2017, and from August 2017 to December 2018 (data available in late 2019).

Poisson regression is used to estimate the relative change in outcome variables. This change is explored through several alternative models, comparing the intervention group to the control group or to each other over time. In addition, we are investigating the differences in the ability to diagnose groups that are at high risk for acquiring HIV (MSM, SAMs, people who inject drugs, and others) and timely diagnosis (represented by CD4-cell count in three categories: less than 200 cells/mm^3^, 200-350 cells/mm^3^, and above 350 cells/mm^3^) across time periods and interventions.

To quantify the level of uncertainty associated with the estimates, Poisson regression models will be fitted to the data using Bayesian modeling under weakly informative priors. For each parameter, we will report the 90% central credible interval from the marginal posterior distribution.

Within the process evaluation, survey data are analyzed descriptively to compare groups with different intervention exposures in terms of self-perceived effects of the intervention levels such as gains in knowledge, self-efficacy to test, and future intention to use the intervention tools.

Qualitative data collected through telephone interviews are analyzed inductively. Using NVivo 8 (QSR International), a data-driven codebook will be established according to the principles of thematic analysis [31].

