## Discussion

This study will deliver useful information on the implementation and effectiveness of an intervention to promote HIV testing among GPs in Flanders. The participatory intervention development strategy allows for a high degree of tailoring of the intervention to the needs of primary care providers. This should lead to a sustainable intervention [32] with high intervention effectiveness [33]. Systematically collected experiences on disseminating and adopting the HIV-testing advice can inform further development of national HIV-testing policies, sexual health strategies, and GPs’ respective roles in these. Yet, this approach of a real-life intervention trial has its limitations: spill-over effects among intervention levels may occur, as GPs not included in the respective intervention condition may download the advice from the GP umbrella organization’s website or may attend training events of a neighboring HAK. The influence of other initiatives to promote HIV testing cannot be excluded, for example, media messages on HIV testing or HIV prevention. Information on the background of GPs not affiliated to a GP circle is lacking and may cause a selection bias.

The use of surveillance data for analysis, however, provides an opportunity to evaluate a real-life intervention including all Flemish GPs. The formative research indicated this as the most feasible data collection method, enabling long-term follow-up while not overburdening busy GPs. However, such routine data are only collected once a year, therefore causing a delay in data access. Detailed information on specific HIV-testing conditions in primary care practices and profiles of testers cannot be collected. Privacy issues impede further subanalyses (eg, sociodemographic characteristics of GPs associated with diagnosis of HIV). In addition, other interventions, such as the introduction of preexposure prophylaxis (PrEP) on a national scale in June 2017 might cause changes in the demand for HIV testing and subsequently in the number of HIV diagnoses, making comparisons over time difficult.

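### The protocol gives conflicting contrasts for the primary outcome and does not name the randomised, period-adjusted comparison with control as the primary one

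*Protocol article*

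**What the plan says.** Four statements in the protocol article bear on how the primary outcome will be compared.

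- Objectives and Outcomes sets the aim, which is to "evaluate the effectiveness of two different intervention levels (dissemination of the information tool and group-level training) against a control condition". The primary outcome sentence that follows then says the change in new GP diagnoses will be evaluated "by comparing the data from 2016, which serve as baseline data, to data from 2017 and 2018". No control group appears in that sentence.
- Data Analysis and Statistical Methods opens by saying that "the distribution of results across unexposed observation periods is compared with that across the exposed observation periods". No calendar-time term is mentioned.
- The next sentence of that section says that "primary and secondary outcomes at the three levels are compared against each other at three different time periods". This is a concurrent comparison of the randomised arms.
- The section then turns to Poisson regression: "This change is explored through several alternative models, comparing the intervention group to the control group or to each other over time". No model is called primary.

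On the design, the Study Design section says the clusters of both intervention levels are unexposed for about two months, and "then all the participants receive the HIV-testing advice online". Level 2 is offered training later, and a control condition is kept to the end. The Randomization Strategy section allocates 25, 25 and 26 clusters. The Discussion cites the national introduction of PrEP in June 2017 as "making comparisons over time difficult".

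**The concern.** These contrasts answer different questions. The one written into the primary outcome is before-after, while the objective above it is a comparison with control.

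The design makes the difference matter. In a classical stepped wedge, clusters cross over at staggered times, so exposure and calendar time can be separated within the exposed clusters. Here both intervention levels receive the advice together, and their crossover cannot do this. The retained control clusters are the only source of information on what would have happened after March 2017 without the advice.

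An estimate that leaves those clusters out, or mixes their later periods with everyone's earlier ones, attributes some of any secular change to the intervention. With several models open and none primary, such an estimate could be reported as the main result while still following the protocol.

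**Working it through.** The protocol gives no event rate, effect size or power figure on this point, so there is no figure of its own to reproduce. What follows illustrates how much secular change each contrast would carry.

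**Inputs from the protocol article**
- Clusters: 25 + 25 + 26 = 76 (Randomization Strategy). The intervention clusters number 50.
- Periods: before March 2017; March to August 2017; August 2017 to December 2018 (Data Analysis and Statistical Methods). August appears in two periods; I count it in the third.
- Baseline year 2016 (Objectives and Outcomes).

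**Assumptions**
- Monthly data from January 2016 to December 2018, giving periods of 14, 5 and 17 months.
- Equal rates per cluster-month and no true intervention effect.
- A secular rate ratio t common to all arms, starting in March or in August 2017. The protocol gives no value for t; I use 0.8 to 1.2.

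**Cluster-months**
- Unexposed: 76×14 + 26×22 = 1,064 + 572 = 1,636, of which 1,064 (65%) lie before March 2017.
- Exposed: 50×22 = 1,100, none before March 2017.

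**(a) 2016 versus 2017 and 2018**
- March onset: (2 + 22t)/24. With t = 0.8: 19.6/24 = 0.817.
- August onset: (7 + 17t)/24. With t = 0.8: 20.6/24 = 0.858.

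**(b) Exposed versus unexposed, no period term**
- March onset: t ÷ [(1,064 + 572t)/1,636]. With t = 0.8: 0.8/0.930 = 0.860.
- August onset: [(5 + 17t)/22] ÷ [(1,194 + 442t)/1,636], where 1,194 = 1,064 + 26×5 and 442 = 26×17. With t = 0.8: 0.845/0.946 = 0.894.

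**(c) Arm by period.** The change in the intervention clusters is divided by the change in the control clusters. A common factor cancels, so the ratio is 1.00 for any t. A Poisson fit with arm, period and exposure terms to the expected counts also gave 1.00 throughout.

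| Assumed t | (a) Before-after | (b) Exposed/unexposed | (c) Arm by period |
|---|---|---|---|
| 0.8 | 0.82–0.86 | 0.86–0.89 | 1.00 |
| 0.9 | 0.91–0.93 | 0.93–0.95 | 1.00 |
| 1.1 | 1.07–1.09 | 1.05–1.06 | 1.00 |
| 1.2 | 1.14–1.18 | 1.10–1.12 | 1.00 |

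Each range runs over March and August onset. For a 20% fall starting in June 2017, the month given for PrEP, contrast (a) is (5 + 19×0.8)/24 = 0.84. Contrast (b) is [(3 + 19×0.8)/22] ÷ [(1,064 + 26×3 + 26×19×0.8)/1,636] = 0.827/0.940 = 0.88.

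**The case against.** The strongest reply is that a controlled comparison is already planned. The Abstract and the objective both set the two levels against a control. The sentence straight after the exposed/unexposed one compares the three randomised levels in the same periods and names the primary outcome. The alternative models are worded as comparisons between groups over time. On that reading, 2016 merely supplies the baseline for the change, and the exposed/unexposed sentence is a generic description of a stepped-wedge design. Period and cluster terms may stand in a full protocol or analysis plan that is not shown.

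Much of this stands. A reader might infer that the primary outcome is planned purely as an uncontrolled comparison, so that any secular change would be read as intervention effect. The documents do not support that. The randomised comparison is in the text, and the exposed/unexposed contrast lets through only part of a trend because later control periods count as unexposed. Nor is the Discussion wrong to list PrEP as a limitation; it does not say that the control arm is ignored.

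The size is also illustrative. The trend is assumed, and equal rates per cluster are a simplification, since the Randomization Strategy section says that the sub-Saharan African migrant population is unevenly spread. The March 2017 crossover fits the analysis periods and the two-month unexposed phase, but Study Duration puts the start of implementation in December 2017, whereas the Abstract and Results put it in January 2017. A different common date would change the ratios, but not the fact that the intervention clusters cross over together.

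What the reply does not remove is the conflict in this document. The contrast attached to the primary outcome names no control, two further contrasts follow, and nothing says which governs. That is a matter of stated wording, not of missing model detail.

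**Conclusion.** The concern holds as a conflict between stated contrasts. It does not show that the trial lacks a controlled analysis. If the 2016 versus 2017 and 2018 estimate is taken as the effect, it carries most of any secular change: 17/24 (71%) to 22/24 (92%) for August and March onset. The unadjusted exposed/unexposed estimate carries part of it, about 53% to 70% of an assumed 20% fall ((1 − 0.894)/0.2 and (1 − 0.860)/0.2). The arm-by-period contrast carries none, provided the change is common to the arms. These shares rest on the assumptions listed in the working. The direction of any actual bias is unknown, because the protocol does not say whether diagnoses would rise or fall. The randomised comparison is the study's main protection against this bias, so the protocol should make it primary.

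**What to change.** Reword Objectives and Outcomes and Data Analysis and Statistical Methods to agree on one primary analysis: a single Poisson model for GP diagnoses with cluster terms, calendar-period terms, an offset for months of observation, and time-varying indicators for advice and for training. Name two primary estimates from it, each against concurrent control clusters: level 1 versus control (the advice term) and level 2 versus control after training (the advice and training terms together). Keep the planned Bayesian fit and credible intervals. Report the 2016 versus 2017 and 2018 and the pooled exposed/unexposed comparisons as descriptive only. Add to the Discussion that a change common to all arms, such as national PrEP, cancels in the primary contrast, whereas one that differs between arms does not. Reconcile the implementation start dates so that exposure can be coded without ambiguity.

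The cost is the wording of two sections and one model specification. No new data are needed, because the Data Collection section already links diagnoses to cluster and intervention level.
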